### Participants

The inclusion criteria are (1) patients of 50 years or over, (2) scheduled to undergo upper abdominal or noncardiac thoracic surgery with expected duration of 2 hours or longer. For those who undergo thoracoscopic or laparoscopic surgery, the expected length of incision must be 5 cm or more, and (3) judged to be at high risk of PPCs according to the ARISCAT risk score (cumulative ARISCAT risk score ≥ 45, see Table 1).

**Table 1 Tab1:** ARISCAT (Canet) risk index

Independent predictors of risk for PPCs		Risk score
Age, years		
≤ 50		0
51–80		3
> 80		16
Preoperative SpO_2_, %		
≥ 96%		0
91–95%		8
≤ 90%		24
Respiratory infection in the last month		
No		0
Yes		17
Preoperative anemia (HbO_2_ ≤ 10 g/dl)		
No		0
Yes		11
Surgical incision		
Peripheral		0
Upper abdominal		15
Intrathoracic		24
Duration of surgery, hours		
≤ 2		0
2–3		16
> 3		23
Emergency procedure		
No		0
Yes		8
Risk class	Number of points in risk score	Pulmonary complications rates
Low risk	<26 points	1.6%
Intermediate risk	26–44 points	13.3%
High risk	≥45 points	42.1%

*PPC* postoperative pulmonary complications

Patients who meet any of the following criteria will be excluded: (1) American Society of Anesthesiologists (ASA) physical classification ≥ IV or the expected survival duration ≤ 24 hours; (2) preoperative history of moderate-to-severe symptomatic prostatic hypertrophy or narrow-angle glaucoma; (3) history of myocardial infarction, severe heart dysfunction (New York Heart Association functional classification ≥ 3) or tachyarrhythmia within 1 year; (4) inhalation of β2-receptor activator, M-receptor blockers and/or glucocorticoids within 1 month before surgery; (5) severe renal dysfunction (requirement of renal replacement therapy) or severe hepatic dysfunction (Child-Pugh grade C); (6) history of acute stroke within 3 months before surgery; (7) unable to cooperate in the inhalational therapy; (8) participation in other clinical trial during the last month or within the six half-life periods of the study drug used in the last trial; or (9) refuse to participate in the study.

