### Patient follow-up and outcome assessment

Patients will be followed up twice daily until postoperative day 2, once daily from postoperative days 3 to 6, and then weekly until 30 days after surgery. Intraoperative data including type and duration of anesthesia, uses and doses of anesthetics, analgesics and other drugs, parameters of mechanical ventilation, fluid balance and transfusion of blood products, as well as type and duration of surgery will be collected. The final cumulative ARISCAT risk score will be calculated just after the surgery. Postoperative data including NRS pain scores, analgesic consumption, respiratory management, return of gastrointestinal function, start of nutrition, occurrence of complications and related treatment, admission to the ICU, duration of hospital stay, and any events that lead to return or readmission to hospital after hospital discharge will be recorded. Any adverse events or complications that occur during the study period will be promptly treated according to routine practice. For patients who deviate from the intervention protocol, deviations will be corrected when possible and follow-up will be completed. For patients who withdraw consent, the last follow-up results will be regarded as the final results.

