#### Outcome analysis

Primary outcome (the incidence of PPCs within 30 days after surgery) will be compared with χ2 test. The difference between groups and the 95% confidence interval of the difference will be calculated.

For secondary outcomes, continuous variables with normal distribution will be analyzed using an unpaired *t* test; continuous variables with abnormal distribution or ranked data will be analyzed using Mann-Whitney *U* test; categorical variables will be analyzed using the chi-squared test, continuity correction chi-squared test or Fisher exact test; time-to-event results will be analyzed using the Kaplan-Meier estimator, and the differences between groups will be tested by the log-rank test. Subgroup analyses will be performed according to the type of the surgery (upper abdominal or thoracic).

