## Discussion

This randomized, double-blind, placebo-controlled trial with two-parallel arms is designed to test the hypothesis that prophylactic penehyclidine inhalation can reduce the incidence of PPCs in high-risk patients undergoing major thoracic and upper abdominal surgery.

Identifying patient at high risk of PPCs is the first step of our study in order to guarantee the efficiency of comparison. Various predictive models have been reported to identify patients at high risk of pneumonia, respiratory failure, pulmonary complications, and cardiopulmonary complications after surgery [1]. In the present study, we adopt the ARISCAT risk score to identify high-risk patients [3] because of the following reasons. First, this scoring system is derived from patients undergoing various types of surgery (including thoracic and abdominal surgery) under various type of anesthesia. Therefore, it is suitable for the patient population in our study. Second, the risk indices are convenient to use. Besides the four patient-related factors, the three surgery-related factors can also be known or anticipated before recruitment. Third, the predictive effect of this scoring system has been validated in a recent study [4].

PPCs are a composite of the hospital-acquired respiratory events after surgery. The diagnostic criteria used to define individual PPCs varied among different studies. In the present study, we used the diagnostic criteria used in the ARISCAT study [3]. In addition, we adopt the Clavien-Dindo Classification to categorize PPCs, and those of grade II or above will be used to calculated the incidence of PPCs [12, 13]. For example, patients with a small amount pleural effusion that does not require specified medical management (e.g., diuretics) or intervention (e.g., drain placement) will be excluded from the diagnosis. This will help us to identify PPCs that have impact on the prognosis of patients.

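### The primary analysis is an unadjusted chi-square test that uses neither the preoperative ARISCAT score needed for eligibility nor the randomisation stratum; it is valid but gives up some precision, probably a modest amount

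*Protocol article*

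**What the plan says.** Under Data analysis, Outcome analysis, the protocol article fixes the primary comparison: "Primary outcome (the incidence of PPCs within 30 days after surgery) will be compared with χ2 test". The effect measure follows: "The difference between groups and the 95% confidence interval of the difference will be calculated". No covariate, stratum or adjusted analysis of the primary outcome is named in the article. Type of surgery returns in that section only as a subgroup factor, although the randomisation section makes it the stratification factor.

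Four other statements bear on this:

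- **Participants.** Every patient must be "judged to be at high risk of PPCs according to the ARISCAT risk score", with a cut at 45 points. The items and points are in Table 1.
- **Discussion, on timing.** Besides the patient factors, "the three surgery-related factors can also be known or anticipated before recruitment".
- **Discussion, on the score.** One reason given for choosing ARISCAT is that "the predictive effect of this scoring system has been validated in a recent study".
- **Patient follow-up and outcome assessment.** There is a second version of the score: "The final cumulative ARISCAT risk score will be calculated just after the surgery".

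**The concern.** A predictor of the primary outcome has to be assessed on each patient before randomisation, and it is used only as a yes/no gate. Above the gate the score still varies widely. If risk rises with the score among those enrolled, an analysis that conditions on it gives a narrower interval for the same risk difference from the same patients. The stratification factor is left out of the primary test as well.

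At stake is the width of the primary confidence interval and some power. The planned 360 per group gives almost exactly the 80% target, so any precision gained would count if the number analysed falls near or below 360.

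**Working it through.** **1. The plan's own figure.** Inputs from Sample size calculation: 42.1% against 32.1%, 80% power, one-sided 0.025, 360 per group, 432 after allowance for dropout. The reduction of 10% is read as absolute, because a relative 10% would need 2125 per group.

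With the pooled formula, n = [1.96·√(2·0.371·0.629) + 0.842·√(0.421·0.579 + 0.321·0.679)]² / 0.10² = 366. The unpooled version gives 363. The stated 360 is within 2% of both.

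**2. Unadjusted precision.** V = 0.421·0.579 + 0.321·0.679 = 0.4617; SE = √(V/n); power = Φ(0.10/SE − 1.96).

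- n = 360: SE = 0.0358, power 79.7%.
- n = 432: SE = 0.0327, power 86.4%, 95% CI half-width 6.4 points.

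**3. Spread of the score above the cut.** Adding up Table 1 for non-emergency surgery of more than 2 hours gives eligible totals of 45 to 106 (upper abdominal) and 47 to 115 (thoracic). The range is wide, but patients may cluster: a thoracic patient aged 51–80 with surgery over 3 hours and no other factor scores 24 + 23 + 3 = 50.

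**4. Slope (assumed).** Table 1 gives class rates of 1.6%, 13.3% and 42.1%, that is logits of −4.12, −1.87 and −0.32. With assumed class midpoints this is roughly 0.06 to 0.11 log-odds per point across the whole scale. No slope is given within scores of 45 or more, so 0.03 to 0.10 per point was tried.

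**5. Risk-factor mixes (assumed).** Each starts with half thoracic patients and is then cut at 45.

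| Item | Low | Middle | High |
|---|---|---|---|
| Surgery > 3 h (rest 2–3 h) | 60% | 60% | 50% |
| SpO2 91–95% / ≤ 90% | 10% / 1% | 20% / 2% | 30% / 5% |
| Respiratory infection | 3% | 7% | 15% |
| Anaemia | 3% | 7% | 15% |
| Emergency | 0% | 2% | 5% |
| Age > 80 (rest 51–80) | 3% | 6% | 12% |
| *Resulting score SD* | 5.4 | 7.3 | 9.6 |
| *Resulting share scoring exactly 50* | 59% | 35% | 15% |

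**6. Adjusted precision.** With intercepts set so that the mean risks are 42.1% and 32.1%, V_adj = E[P1(1−P1)] + E[P2(1−P2)] + Var(P1−P2)/2, where P1 and P2 are a patient's risks under the two treatments. The reduction is 1 − V_adj/V. Each cell gives the reduction and the power at 360 per group:

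| Slope per 10 points | Low | Middle | High |
|---|---|---|---|
| 0.3 | 0.6%; 80.0% | 1.1%; 80.2% | 2.0%; 80.5% |
| 0.5 | 1.8%; 80.4% | 3.1%; 81.0% | 5.2%; 81.8% |
| 0.8 | 4.4%; 81.5% | 7.4%; 82.7% | 11.9%; 84.5% |
| 1.0 | 6.5%; 82.3% | 10.8%; 84.1% | 16.8%; 86.5% |

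Mixes with still fewer risk factors (57–75% of patients at exactly 50, SD 4.1–5.3) gave reductions of 0.4% to 1.7% at slopes of 0.3 to 0.5.

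The middle scenarios (middle mix, slopes 0.5 and 0.8) gain 81.0 − 79.7 = 1.3 to 82.7 − 79.7 = 3.0 power points. At 432 per group the same reductions take the half-width from 6.4 to between 6.3 and 6.2 points.

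**The case against.** The strongest reply is that nothing here is an error. A chi-square test with a risk difference is valid in a randomised trial and matches the basis of the sample size. That stands: a reader might infer a biased or invalid primary test, and the article does not support that.

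A reader might also infer that the trial has no reserve of power. That does not follow. Participants keeps dropouts in the intention-to-treat analysis, with the last recorded result carried as final; only rejected cases leave. If nearly all 432 per group are analysed, unadjusted power is about 86%. Power is tight only if a full 20% is lost: 432 × 0.8 ≈ 346 per group, about 78%.

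The size of the gain is open to challenge, and rightly. The Table 1 rates differ between classes, whereas all patients here are in the top class. The steps between the class logits shrink (2.2, then 1.6). This trial also counts only complications of Clavien-Dindo grade II or above, so the slope and the validation found elsewhere need not carry over. The documents cannot exclude a trivial gain, and the top-right end of the range is a corner case.

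It is tempting to add that type of surgery carries almost none of the prognostic information. The calculation cannot show this, because it lets type of surgery act only through the score.

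Finally, Patient recruitment and baseline data collection does not list the preoperative total or expected duration. Storage of the score is likely, since eligibility depends on it, but it is not stated.

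**Conclusion.** The point holds as an efficiency improvement and not as an error. The article fixes an unadjusted primary analysis while requiring, before randomisation, a score that it regards as predictive, and while stratifying on type of surgery. Adjustment gained precision in every scenario tried, but the amount rests on assumed slopes and risk-factor mixes. The variance of the risk difference falls by roughly 0.5% to 17%, most plausibly by a few percent. That is about 1 to 3 power points at 360 per group from a base of 79.7%. The change is worth making because it costs little; the trial's validity does not depend on it.

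**What to change.** In Outcome analysis, before unblinding, make the primary analysis a logistic regression on treatment, type of surgery and the preoperative ARISCAT score. Enter the score as a continuous variable, using expected duration as assessed at eligibility. Standardise the fitted model to the marginal risk difference with its 95% confidence interval and test, so that the effect measure stays the one the article already names. Keep the unadjusted chi-square test and difference as a sensitivity analysis.

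State explicitly that the final score calculated after surgery is not used, because it is determined after randomisation. If the preoperative total was not stored, rebuild it from the recorded baseline components, leaving out actual duration of surgery.

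The cost is one paragraph and a little more analysis work. The downsides are that the estimate becomes model-assisted (in a randomised trial the standardised estimate remains consistent if the model is wrong), that the gain may be small, and that the preoperative score must be retrievable from the eligibility records.

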## Discussion

This randomized, double-blind, placebo-controlled trial with two-parallel arms is designed to test the hypothesis that prophylactic penehyclidine inhalation can reduce the incidence of PPCs in high-risk patients undergoing major thoracic and upper abdominal surgery.

Identifying patient at high risk of PPCs is the first step of our study in order to guarantee the efficiency of comparison. Various predictive models have been reported to identify patients at high risk of pneumonia, respiratory failure, pulmonary complications, and cardiopulmonary complications after surgery [1]. In the present study, we adopt the ARISCAT risk score to identify high-risk patients [3] because of the following reasons. First, this scoring system is derived from patients undergoing various types of surgery (including thoracic and abdominal surgery) under various type of anesthesia. Therefore, it is suitable for the patient population in our study. Second, the risk indices are convenient to use. Besides the four patient-related factors, the three surgery-related factors can also be known or anticipated before recruitment. Third, the predictive effect of this scoring system has been validated in a recent study [4].

PPCs are a composite of the hospital-acquired respiratory events after surgery. The diagnostic criteria used to define individual PPCs varied among different studies. In the present study, we used the diagnostic criteria used in the ARISCAT study [3]. In addition, we adopt the Clavien-Dindo Classification to categorize PPCs, and those of grade II or above will be used to calculated the incidence of PPCs [12, 13]. For example, patients with a small amount pleural effusion that does not require specified medical management (e.g., diuretics) or intervention (e.g., drain placement) will be excluded from the diagnosis. This will help us to identify PPCs that have impact on the prognosis of patients.

Using effective strategies to prevent PPCs is essential in high-risk patients. Some strategies have been proved beneficial in previous studies, such as smoking cessation [14] and inspiratory muscle training [15, 16] before surgery; use of regional anesthesia [17, 18], lung-protective ventilation (for patients who received general anesthesia) [19, 20] and goal-directed fluid therapy [21] during surgery; as well as use of continuous positive airway pressure or noninvasive ventilation [22, 23] and early exercise [24, 25] after surgery. High-risk patients, such as those complicated with bronchial asthma, chronic obstructive pulmonary disease (COPD), pneumonia, left ventricular dysfunction and morbid obesity, tend to develop AHR during the perioperative period [26–28], which increase the risk of PPCs. Whereas anticholinergic inhalation can prevent parasympathetic bronchoconstrictive effect and reduce high airway resistance [29, 30], and improve patients’ pulmonary function [31, 32]. As a long-acting anticholinergic drug with selective M1, M3-receptors blocking activity [10], penehyclidine is a promising candidate agent in the treatment of COPD [33]. Indeed, penehyclidine inhalation was used in COPD patients with acute exacerbation and resulted in good effectiveness [34]. Our pilot study suggested that penehyclidine inhalation might be effective in preventing PPCs in high-risk patients [11]. Results of the present study will provide evidence on the effectiveness and safety of penehyclidine inhalation in preventing PPCs in high-risk surgical patients.

Our study has several limitations. First, unlike other inhalational anticholinergics (such as tiotropium bromide and ipratropium bromide), penehyclidine is currently only approved for clinical use in China. This will restrict the generalizability and reproducibility of our results. However, considering the selective M1 and M3 receptor blocking activity and long-lasting effects, penehyclidine may be more suitable for PPCs prevention. Second, some perioperative factors, such as selection of anesthetic methods, use of anesthetics and analgesics, fluid management, respiratory management and ventilator settings, may also affect the occurrence of PPCs. We do not standardize anesthetic management in the present study. This might produce confounding effects to our intervention. However, large sample size and strict randomization will help to balance these factors between groups. And our results will reflect the impact of penehyclidine inhalation on PPC incidence in the real-world practice.

## Trial status

Recruitment and data collection of patients started on 1 September 2015. The recruitment of 864 patients at high-risk of PPCs is scheduled to end on 1 August 2018. Data analysis and evaluation will be performed subsequently. The final results of this study will be published.

## Abbreviations

AHR: Airway hyperresponsiveness
ASA: American Society of Anesthesiologists
CAM-ICU: Confusion assessment method for the intensive care unit
COPD: Chronic obstructive pulmonary disease
CRFs: Case report forms
ICU: Intense care unit
NPRS: Numeric Pain Rating Scale
PACU: Post-anesthesia care unit
PPCs: Postoperative pulmonary complications
